**Fig. 2 Fig2:**
[figure not shown]
Procedure of single-blind. Take participant No.01001 as an example. (1) The participant was randomly assigned to the test group by REDCap system. (2) The participant’s TCM syndrome type was diagnosed by a TCM physician according to Table 2. (3) The drug administrator selects the correct TCM granules of corresponding type. (4) The sachets of TCM granules were removed from the red box to a white box. (5) The white box was labeled by No.01001 and passed to the participant, who was blinded until the end of the study. (6) The red box was labeled too and kept as evidence of single-blind by the drug administrator

### Sample size calculation

The sample size was calculated by PASS 15.0 software. The model was established according to the log-rank test of survival analysis (bilateral side), with α=0.05 and power 1 – β = 0.8. Based on recent researches [15, 16], the median survival in ES-SCLC with first-line chemotherapy was approximately 8 months, which we estimated to be 4 months longer after TCM combined with chemotherapy. The recruitment period was set as 24 months while the total time was 36 months. The minimum sample size was calculated as 112 in each group. Considering a 10% loss, we sought to enroll at least 270 (135 per group) participants in the study.

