## Methods/design

### Study design

This is a multicenter, randomized, single-blind, placebo-controlled clinical trial, with superiority in the framework. After a run-in period within 7 days, 270 eligible participants will be randomized to the test group (TCM granules with chemotherapy) or the control group (placebo with chemotherapy) in a 1:1 ratio. All participants will undergo a treatment period of 12–18 weeks and a follow-up period until death. During the treatment period, both groups have to receive chemotherapy for 4–6 cycles. In the interphase of chemotherapy (days 6–21 of each cycle), participants in the test group will take TCM granules while those in the control group will take placebo granules for 15 days. Visits will be performed at days 0, 21, 42, 63, 84, 105, and 126 in the treatment period, and the last week of every 3 months (approximately 90 days) during the subsequent follow-up period. The study is scheduled to open from December 2018 to December 2021. The recruiting was started in June 2019 and lasted for 24 months. The endpoint of follow-up is the date of death or December 31, 2021 (Fig. 1).

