## Trial status

The trial is conducted according to the protocol (Version 2.0, 4 June 2019). It is currently enrolling participants. The recruitment began on 20 June 2019 and was expected to be completed on 19 June 2021. The first participant was enrolled on 4 September 2019.

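### The sample size assumes 36 months from first recruitment to cut-off, but the stated dates give 30.4 months, so the claimed 80% power for overall survival is about 75%

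*Protocol article*

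**What the plan says.** The protocol article sizes the trial for a two-sided log-rank test on overall survival, "with α=0.05 and power 1 – β = 0.8". For the control arm it takes it that "the median survival in ES-SCLC with first-line chemotherapy was approximately 8 months". The size of the expected benefit in the test arm is then set in these words: "which we estimated to be 4 months longer after TCM combined with chemotherapy". The time frame in the same section is: "The recruitment period was set as 24 months while the total time was 36 months". The section gives a minimum of 112 per group and, allowing for 10% loss, a target of 270 (135 per group).

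The calendar is given in two other places. Study design says "The study is scheduled to open from December 2018 to December 2021" and "The endpoint of follow-up is the date of death or December 31, 2021". Trial status says "The recruitment began on 20 June 2019 and was expected to be completed on 19 June 2021", and adds that the first participant was enrolled on 4 September 2019. The article gives no later data cut-off and no target number of deaths.

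**The concern.** Recruiting for 24 months within a total of 36 leaves 12 months between the last randomisation and the cut-off. The printed dates leave about half of that. The 36 months match the administrative window from December 2018 to December 2021, whose first six months or so precede recruitment, when no patient is at risk.

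A log-rank test draws its power from the number of deaths. Bringing the cut-off about 5.6 months closer, relative to every patient's entry, removes deaths from the only primary outcome. Patients recruited last would be censored at about 6 months, before either assumed median. A non-significant result from a trial described as having 80% power could then be taken as stronger evidence of no benefit than the design supports.

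**Working it through.** **Inputs from the article**
- Medians 8 and 12 months, so under exponential survival the hazard ratio is 8/12 = 0.667 and ln(12/8) = ln 1.5 = 0.4055.
- Two-sided α = 0.05 (1.96), power 0.80 (0.8416), 1:1 allocation.
- 270 enrolled with 10% loss: 270 × 0.9 = 243 evaluable.

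**Assumptions not in the article:** exponential survival and uniform accrual.

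**Calendar**
- 20 June 2019 to 31 December 2021: 925 days, 30.4 months.
- 19 June 2021 to 31 December 2021: 195 days, 6.4 months.
- 4 September 2019 to 31 December 2021: 849 days, 27.9 months, of which 21.5 are accrual.

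**Formulae**
- Deaths required (Schoenfeld): 4 × (1.96 + 0.8416)² / (ln 1.5)² = 191.
- Probability of death in an arm by the cut-off: 1 − [exp(−λf) − exp(−λT)] / (λA), with λ = ln 2 / median, A the accrual period, T the total time and f = T − A.
- Power with d deaths: Φ(√d / 2 × ln 1.5 − 1.96).

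**Step 1: reproduce the plan's figure (A = 24, T = 36, f = 12)**
- Control, λ = 0.08664: 1 − (0.3536 − 0.0442)/2.0794 = 0.851.
- Test, λ = 0.05776: 1 − (0.5000 − 0.1250)/1.3863 = 0.729.
- Mean 0.790. Deaths: 243 × 0.790 = 192. Power: Φ(2.81 − 1.96) = 80.2%.
- Per group: 191/(2 × 0.790) = 121, and 121/0.9 rounds up to 135, the printed enrolment. So 243 evaluable is the basis on which the stated 80% and the 270 agree.

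**Step 2: use the printed dates (A = 24, T = 30.4, f = 6.4)**
- Control: 1 − (0.5743 − 0.0718)/2.0794 = 0.758.
- Test: 1 − (0.6910 − 0.1727)/1.3863 = 0.626.
- Mean 0.692. Deaths: 243 × 0.692 = 168, which is 24 fewer. Power: Φ(2.63 − 1.96) = 74.8%.

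Other methods agree for the 30.4-month calendar: Lakatos 74.7%, Lachin-Foulkes 74.0%, Freedman 73.7%, and a log-rank simulation with 121 per arm about 74.8%.

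**Step 3: vary how losses are counted**

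| Basis | Power, 36 months | Power, 30.4 months |
|---|---|---|
| 112 per group, as printed | 77.0% | 71.4% |
| 243 evaluable | 80.2% | 74.8% |
| 270, with 10% lost as exponential censoring | 81.1% | 75.9% |
| 270, nobody lost | 84.2% | 79.2% |

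Each row loses 5.0 to 5.6 points.

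**Step 4: count accrual from the first enrolment (A = 21.5, T = 27.9)**
- With 243 evaluable: about 163 deaths and 73.6%. This assumes that all 270 are still recruited by 19 June 2021.

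**Step 5: what would restore 80%**
- With 243 evaluable, 191 deaths are expected about 11.7 months after the last randomisation, about June 2022.
- With the December 2021 cut-off, about 138 evaluable per arm would be needed, or about 154 per arm (308 in total) after 10% loss.

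**The case against.** The date conflict is not in dispute. The case on the other side concerns its size and the remedy.

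- **The 75% depends on the basis.** Using 243 treats the 27 lost patients as contributing nothing, although the withdrawal criteria ask that withdrawn participants be followed where possible until the endpoint. Many could still contribute to overall survival, and with no loss power is 79.2%. This stands as a caution about the exact figure. It does not remove the shortfall: the same basis gives 84.2% at 36 months, and even this most favourable case is below 80%.
- **Not all of the gap on the 112 basis comes from the calendar.** That is right. The printed 112 per group gives only 77.0% at 36 months, and 112/0.9 is 125, not 135. It is a separate discrepancy, and this point does not rest on it.
- **The late first enrolment is a matter of conduct.** It leaves the last patient's 6.4 months unchanged and costs about one further point. It is therefore shown only as a sensitivity case. The close of recruitment is also an expected date.
- **The loss is moderate.** A shortfall of about 5 points does not bias the estimate or inflate type I error, and a confidence interval would show the precision achieved. That is fair, but the stated power for the sole primary outcome is still not what the printed calendar delivers.
- **An event-driven cut-off has no natural end, and the target depends on the formula** (191 by Schoenfeld, 197 by Freedman). This stands as a drafting point: if losses exceed 10% or survival is longer than assumed, 191 deaths could come later than June 2022.

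**Conclusion.** The point holds. The sample size rests on 36 months in total and 12 months' minimum follow-up, while the article's own dates give 30.4 and 6.4 months. On the basis that reproduces the stated 80%, expected deaths fall from 192 to 168 and power from 80.2% to 74.8%, so the type II error rises from about 20% to about 25%. Across the ways of counting losses, power under the printed calendar lies between 71.4% and 79.2%. These power figures assume exponential survival and uniform accrual; the date conflict needs neither assumption. Because it concerns the only primary outcome and can be put right cheaply, it should be corrected.

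**What to change.** **Preferred.** Replace the fixed cut-off of 31 December 2021 for overall survival with: when 191 deaths have been observed, or 12 months after the last randomisation, whichever is later. Under the plan's assumptions with 243 evaluable patients this falls at about June 2022. Naming a latest date would keep the rule from running on if deaths come more slowly than assumed. A plain cut-off 12 months after the last randomisation is simpler and restores the follow-up that the calculation assumed, with about 192 expected deaths. The cost is a protocol amendment and about six more months of survival status on the existing 3-monthly schedule, with no new patients.

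**If the date cannot move.** Restate the sample size section with 24 months' accrual plus 6.4 months' minimum follow-up, about 168 expected deaths and about 75% power, and name the assumptions and the number of evaluable patients used. This costs one sentence.

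In either case, state that total time in the calculation runs from the opening of recruitment to the data cut-off, so that it is not confused with the administrative window that begins in December 2018.

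### The sample-size chain is inconsistent as printed: 112 per group is not reproduced by the stated inputs (121 to 125), and 10% loss on 112 gives 124 or 125, not 135

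*Protocol article*

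**What the plan says.** The section headed Sample size calculation in the protocol article bases the calculation on a two-sided log-rank test run in PASS 15.0, "with α=0.05 and power 1 – β = 0.8". For the control arm it says that "the median survival in ES-SCLC with first-line chemotherapy was approximately 8 months", and for the test arm gives a median "which we estimated to be 4 months longer after TCM combined with chemotherapy", that is, 12 months. On timing: "The recruitment period was set as 24 months while the total time was 36 months". Allocation is 1:1 (Study design).

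The results are given in two steps: "The minimum sample size was calculated as 112 in each group", followed by "Considering a 10% loss, we sought to enroll at least 270 (135 per group) participants in the study". The section gives no number of deaths, accrual pattern, survival distribution or drop-out hazard.

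**The concern.** The section prints nearly every input that a log-rank sample size needs, so a reader can check it. Two links fail. The 112 is lower than standard methods give for those inputs, and the 135 is higher than a 10% allowance on 112 gives.

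The 112 is presented as the minimum that secures 80% power for overall survival, the primary outcome. Anyone who later judges whether enough evaluable participants remain would use that figure. Read with the target of 135, it suggests that the trial can lose 17% per group and keep its power. On the printed inputs it cannot.

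**Working it through.** **Inputs.** From Sample size calculation: control median 8 months, test median 12 months, two-sided alpha 0.05, power 0.80, recruitment R = 24 months, total T = 36 months. From Study design: 1:1 allocation. Assumed here, because the article states neither: exponential survival and uniform accrual.

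**Hazards.** ln 2 / 8 = 0.0866 and ln 2 / 12 = 0.0578 per month. Hazard ratio = 8/12 = 0.667.

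**Deaths required.** (1.960 + 0.842)² = 7.849.
- Schoenfeld: 4 × 7.849 / (ln 1.5)² = 31.40 / 0.1644 = 191.0.
- Freedman: (1.667/0.333)² × 7.849 = 25 × 7.849 = 196.2, rounded up to 197.

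**Probability of death by month 36.** With uniform accrual, p = 1 − [exp(−λ(T−R)) − exp(−λT)] / (λR).
- Control: 1 − (0.3536 − 0.0442) / (0.0866 × 24) = 0.851.
- Test: 1 − (0.5000 − 0.1250) / (0.0578 × 24) = 0.729.
- Sum 1.581, mean 0.790.

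**Attempt to reproduce the 112** (n per group = deaths / 1.581).

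| Method | n per group |
|---|---|
| Schoenfeld | 191.0 / 1.581 = 120.8, so 121 |
| Lakatos-type log-rank | 121.1, so 122 |
| Lachin-Foulkes | 123.6, so 124 |
| Freedman | 196.2 / 1.581 = 124.1, so 125 |

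No method gives 112. Other readings of the printed inputs also miss it:

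| Reading | n per group |
|---|---|
| One-sided test | 96 to 99 |
| Everyone followed for 36 months | 105 to 108 |
| Fixed 24-month follow-up | 118 to 122 |
| 24 months' accrual plus 36 months' follow-up | 100 to 103 |
| 10% loss entered as a hazard | 124 to 135 |

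**Power at 112 per group.** Expected deaths: 112 × 1.581 = 177. Power is 77.0% (Schoenfeld), 76.9% (Lakatos-type) or 75.8% (Freedman).

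**The loss step, which needs no survival assumption.**
- 112 / 0.9 = 124.4, so 125 per group (250 in total).
- 112 × 1.1 = 123.2, so 124 per group.
- Implied loss from 135 to 112: 1 − 112/135 = 17.0%.
- 112 × 1.2 = 134.4, so 135 also matches a 20% mark-up.
- 121 / 0.9 = 134.4, so 135 is what 10% loss gives on the recomputed minimum.

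**Power of the enrolment target.** 135 × 0.9 = 121.5 per group, and 121.5 × 1.581 = 192 deaths. Power is 80.2% (Schoenfeld) or 79.2% (Freedman).

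**Sensitivity to rounding of the medians** (Schoenfeld, all else as printed). Medians of 7.7 and 11.7 months give 112.2 per group; 8 and 12.2 months give 111.9.

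**The case against.** The strongest reply is that 112 may be a correct software result from inputs that the article rounds or omits. The control median is given only as approximate, and small changes to the medians bring the Schoenfeld result to 112. With 7.7 and 11.7 months, 112 per group has 79.9% power. Accrual weighted towards the start of the 24 months would also lower the requirement. This stands: the article shows that 112 is not reproducible as printed, not that the software run was wrong. It does not rescue the loss step, which uses only 112, 10% and 135.

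A second reply is that the harm is hypothetical. No passage says that 112 evaluable per group will be accepted or that 17% loss is tolerable. The target is worded as a floor, and the withdrawal criteria ask that withdrawn participants be followed where possible until the endpoint, so withdrawal need not cost deaths. This also stands and limits the point to a misreported chain.

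Two stronger readings are tempting. A reader might infer that the trial is underpowered because its minimum is too low. The documents do not support this on the printed 36-month inputs, since the target is 270 and that number less 10% gives about 79 to 80% power. A reader might also infer that 112 betrays a shorter accrual period in the calculation. About 12 months' accrual in 36 does give roughly 110 to 113, but so do slightly different medians, so the source of the figure cannot be identified.

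**Conclusion.** The point holds as an inconsistency in the stated figures. On the printed inputs the minimum is 121 to 125 per group, 8 to 12% above 112, and 112 per group has 76 to 77% power in place of 80%. These figures rest on exponential survival, uniform accrual and medians of exactly 8 and 12 months. The second inconsistency rests on no assumption: 10% loss on 112 gives 124 or 125 per group, not 135.

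The two discrepancies offset each other, because 135 is what 10% loss on 121 requires. That makes the 112 the likelier slip, but only the PASS output can settle it. The consequence is confined to the intermediate figure or the loss rate.

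**What to change.** Retrieve the PASS procedure and its inputs, then restate the chain in one of two ways:

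- If the medians were 8 and 12 months with uniform accrual, replace 112 by about 121 evaluable per group (191 deaths) and keep the 10% loss: 121 / 0.9 = 134.4, so 135 per group.
- If 112 is the true output, print the exact medians and accrual pattern that produce it, and correct the loss allowance to about 17%.

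In either case state the required number of deaths. Do not add a statement of 12 months' minimum follow-up, although 36 − 24 implies it, until it is reconciled with the dates elsewhere. Trial status expects recruitment to end on 19 June 2021 and Study design ends follow-up on 31 December 2021, which leaves about 6.4 months for the last participant. That mismatch is a separate question and is not part of the size given here. Making the analysis depend on reaching a number of deaths would likewise be a design change against the fixed end date, and this correction does not need it.

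The cost is a check of the software record and a change of wording. The enrolment target stays at 270. The only downside is that a published figure has to be corrected.

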### Assessments and time-points

Assessments will be performed at baseline and every protocol-defined interval (Table 2) until the occurrence of death or study completion.

**Table 2 Tab2:** Schedule of data collection

	Screening and baseline	Treatment period						Follow-up period			
**Visits**	**--**	**1**	**2**	**3**	**4**	**5**	**6**	**7**	**8**	**9**	**……**
**Time points (days)**^**a**^	**− 7 to 0**	**21**	**42**	**63**	**84**	**105**	**126**	**195**	**285**	**375**	**……**
**Time windows (days)**	**--**	**±7**	**±7**	**±7**	**±7**	**±7**	**±7**	**±21**	**±21**	**±21**	**±21**
Informed consent	×										
Inclusion and exclusion criteria	×										
Survival state		×	×	×	×	×	×	×	×	×	×
General data	×										
History of diagnosis and treatment	×										
ECOG-PS	×										
Imaging examination	×		×		×		×	×	×	×	×
ORR			×		×		×	×	×	×	×
FACT-L scale	×	×	×	×	×	×	×	×	×	×	×
TCM symptoms scale	×	×	×	×	×	×	×	×	×	×	×
Tumor markers	×	×	×	×	×	×	×				
Blood, urine, stool routine examination	×	×	×	×	×	×	×				
Liver and renal function examination	×	×	×	×	×	×	×				
Electrocardiogram	×	×	×	×	×	×	×				
AEs		×	×	×	×	×	×	×	×	×	×
Compliance assessment		×	×	×	×	×	×	×	×	×	×
Drug combination		×	×	×	×	×	×	×	×	×	×

*Abbreviations: ECOG-PS* Eastern Cooperative Oncology Group performance status, *ORR* objective response rate, *FACT-L* Functional Assessment of Cancer Therapy-lung carcinoma, *TCM* traditional Chinese medicine, *AEs* adverse events

^**a**^At the end of each cycle in the treatment period and every 3 months in the follow-up period

#### Primary outcome

The primary outcome is overall survival (OS), from randomization to death.

#### Secondary outcomes

The secondary outcomes are as follow:

PFS: From randomization to occurrence of imaging-based disease progress (PD), which is assessed by the investigators.

ORR: Imaging examinations for the target lesions will be done at days 0, 42, 84, and 126 during the treatment period and every 90 days during the follow-up period. The tumor response is evaluated according to standards of Response Evaluation Criteria in Solid Tumors (RECIST) Version 1.1, rating as complete response (CR), partial response (PR), stable disease (SD), or PD. ORR is the ratio of participants rated as CR and PR to total cases.

QoL: Functional Assessment of Cancer Therapy-lung carcinoma (FACT-L) scale and TCM syndromes scale are used for the evaluation of QoL. The participants will answer the questionnaires in FACT-L independently with the assistance of investigators, covering physical, social and family, emotional, and functional statuses, as well as lung cancer module. The total score of FACT-L is calculated by adding up the scores of each item. TCM syndrome scale is designed to record the extent of several typical symptoms such as cough, phlegm, fatigue, shortness of breath, and loss of appetite. 0, 1, 2, and 3 points represent “none”, “mild”, “moderate”, and “severe”, respectively. QoL data are collected at baseline and in each visit.

Tumor markers: the commonest tumor markers, NSE and proGRP, are tested at days 0, 21, 42, 63, 84, 105, and 126 during the treatment period.

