**Method/design:**

A multicenter, randomized, single-blind, placebo-controlled clinical trial will be conducted to determine whether the TCM granules combined with chemotherapy can improve the OS of ES-SCLC. Two hundred seventy participants will randomly receive 4–6 cycles (21 days per cycle) of chemotherapy plus TCM granules or placebo. The primary outcome measure is OS. The secondary outcome measures includes progression-free survival (PFS), objective response rate (ORR), quality of life (QoL), and tumor markers. Visits will be performed at the end of each cycle during the treatment period and then every 3 months in the follow-up period until the patients’ death or study completion.

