## Background

Small-cell lung cancer (SCLC) is an aggressive and rebellious neuroendocrine carcinoma, which accounts for approximately 12–15% of lung cancer [1]. More than half of the newly diagnosed SCLC patients have developed into the extensive stage (ES), with lesions beyond the boundaries of hemithorax, whose 2-year mortality exceeds 95% [2]. In the past three decades, platinum-based chemotherapy, the first-line regimen of ES-SCLC has stagnated in the median progress-free survival (PFS) of 9–11 months, which is far from meeting the cure needs [3]. Even if the chemo-periods prolonged or dosages enhanced, the limited improvement in PFS and the same overall survival (OS) would come at the expense of more severe adverse events [4, 5], probably leading to the interruption of treatment [6]. The landmark breakthrough appeared in the treatment of ES-SCLC until the IMpower 133 and CASPIAN, adding the immune-checkpoint inhibitors (ICIs) to the standard etoposide and platinum [7]. Although this combination also tends to a heavier treatment burden because of its overprices and immune-related adverse reactions [8, 9], it does inspire a strategy for combining multiple treatments to benefit more ES-SCLC, especially on the grounds of chemotherapy, as some studies have tried [10, 11]. Thus, it is of great value to enrich the first-line regimens of ES-SCLC if therapy with better practicability and cost-effectiveness can be found in cooperation with chemotherapy.

Through a series of meta-analysis, traditional Chinese medicine (TCM) has been shown to improve the efficacy and safety with chemotherapy in varieties of malignancies, such as breast cancer [12], colorectal cancer [13], and non-small cell lung cancer [14]. TCM regimens have also increasingly widely used in the clinical practice of ES-SCLC for its synergy with chemotherapy. In previous researches [15], the long-term and regular TCM regimens were preliminarily considered as a favorable prognosis factor of ES-SCLC. Unfortunately, due to the small sample size and substandard design, no study so far has provided a clear-cut answer to whether TCM regimen can synergize chemotherapy to achieve longer oncologic survival of ES-SCLC. Therefore, we organized a randomized controlled trial (RCT) with relatively high-quality to verify the prognostic value of TCM on ES-SCLC.

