### Statistical analysis

All data will be processed by a two-sided statistical test in SAS software 9.2 (the installation site’s authorization number: 11202165). *P*≤0.05 is defined as a statistical significance. Full analysis set (FAS), per-protocol set (PPS), and safety set (SS) will be created after data collection.

The statistical design is as follows:

For characteristics at baseline, continuous variables will be described with the use of mean (standard deviation) or median (quartile) based on the distribution. A T-test will be adopted if the normality and homogeneity of variance are satisfied; otherwise, the nonparametric test will be carried out. Categorical variables will be analyzed by the chi-square test or nonparametric test.

For OS and PFS, the Kaplan-Meier curve and the Log-rank test will be used to analyze the distribution of the survival function. And the factors selected in the univariate analysis will be brought into the Cox regression for further multivariate analysis.

For tumor response, the logistic regression or Ridit analysis will be used to compare the differences in ORR, while the proportion of CR, PR, SD, and PD will be compared by the CHM test because of the central effect.

For QoL and tumor markers, the T-test or RMANOVA will be used to compare the differences intra- or inter-groups if the two groups’ scores at baseline are similar. Or the covariance analysis will be used to correct for confounders if not.

For safety assessment, the AEs and their incidences should be recorded in detail.

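### PFS is defined by imaging progression alone, without death, so as written it is a time to progression carrying the PFS name

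*Protocol article*

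**What the plan says.** Under Secondary outcomes, the protocol article gives the start, the event and the assessor: "PFS: From randomization to occurrence of imaging-based disease progress (PD), which is assessed by the investigators". The OS definition just before it reads "The primary outcome is overall survival (OS), from randomization to death". The Statistical analysis section treats both endpoints alike: "For OS and PFS, the Kaplan-Meier curve and the Log-rank test will be used to analyze the distribution of the survival function". No section counts death as a PFS event, gives a PFS censoring rule or names a competing-risk method.

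PFS is secondary: "The secondary outcome measures includes progression-free survival (PFS), objective response rate (ORR), quality of life (QoL), and tumor markers". Imaging is scheduled at days 42, 84 and 126 on treatment and "every 90 days during the follow-up period". Table 2 places the first follow-up visits at days 195, 285 and 375, each ±21 days. Survival state is recorded at every visit after baseline, and the schedule runs on: "Assessments will be performed at baseline and every protocol-defined interval (Table 2) until the occurrence of death or study completion".

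**The concern.** Progression-free survival normally ends at progression or death, whichever comes first. Here only progression seen on imaging ends it. A participant who dies before a scan shows progression contributes no event. In a Kaplan-Meier or log-rank analysis such a participant would most naturally be censored, that is, treated as someone who could still progress later at the same rate as those who remain. In a disease for which the Background puts 2-year mortality above 95%, dying and progressing are closely linked, so that assumption is doubtful.

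Three things are at stake:

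- **Medians.** The reported median would be too long in any arm that has such deaths. The curve could even lie above the OS curve, which a true PFS curve cannot do.
- **Treatment comparison.** The log-rank test would compare rates of documented progression only. An effect of the granules on early death, in either direction, would not show in this endpoint.
- **Comparability.** The article discusses PFS from other studies. Results under this definition could not safely be set beside figures that count deaths; how far they would differ depends on how many deaths are left out.

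**Working it through.** The article states no PFS median, event count or power, so there is no figure to reproduce. The check has two parts.

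**1. Reading the definitions together.** OS runs to death and death is named. PFS runs to imaging progression and death is not named. The analysis sentence applies the same methods to both and adds no rule that would bring death into PFS. Taken as written, the PFS event is progression only.

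**2. Illustrating the size.** All inputs here are assumptions; the article supplies none of them. Hazards are constant, and f is the share of first events in an arm that are deaths without documented progression.

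*Median within an arm.* Let the total hazard of progression or death be λ. The true PFS median is ln 2 / λ. With those deaths censored, only the progression hazard (1 − f)λ drives the curve, so its median is ln 2 / [(1 − f)λ]. The overstatement is 1/(1 − f) − 1:

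| f in the arm | Overstatement | A true median of 6 months (assumed) reads as |
|---|---|---|
| 10% | 1/0.90 − 1 = 11% | 6.7 months |
| 20% | 1/0.80 − 1 = 25% | 7.5 months |
| 30% | 1/0.70 − 1 = 43% | 8.6 months |

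*Hazard ratio between arms.* With f taken in the control arm, the PFS hazard ratio is (1 − f) × HR for progression + f × HR for death without progression. Assume a progression HR of 0.75 and a death HR of 1.0:

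- f = 20%: 0.80 × 0.75 + 0.20 × 1.0 = 0.80
- f = 30%: 0.70 × 0.75 + 0.30 × 1.0 = 0.825

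The progression-only analysis returns 0.75 in both cases. With f = 20% and an assumed death HR of 2.0, the PFS hazard ratio is 0.80 × 0.75 + 0.20 × 2.0 = 1.00, and the written definition still returns 0.75.

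*The two arms do not share one f.* In the scenario with f = 20% in control and a death HR of 1.0, the test arm has f = 0.20/0.80 = 25%. The overstatement of the median is then 25% in control and 1/0.75 − 1 = 33% in test. The inflation table must therefore be read arm by arm.

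**The case against.** The best counter-argument is that the article condenses a fuller protocol (Version 2.0, not shown), that the endpoint is called progression-free survival throughout, and that the single line may be a shortened form. Event and censoring details are often left to the fuller documents. Part of this stands: censoring is a consequence drawn from the stated event and the stated method, and the article does not itself say it. But the article is not silent on the event. It defines it, and the definition is wrong for the name. An analysis plan that followed the sentence would carry the error forward, and one that corrected it would disagree with the published protocol.

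A reader might be tempted by four stronger conclusions. The document supports none of them.

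- **That deaths without documented progression will be common.** The planning assumption is that "the median survival in ES-SCLC with first-line chemotherapy was approximately 8 months, which we estimated to be 4 months longer". Exponential survival with medians of 8 and 12 months gives 1 − 2^(−2.957/8) = 23% and 1 − 2^(−2.957/12) = 16% dying within 90 days (2.957 months). These are deaths among all living participants, many of whom would already have progressed, so they do not estimate f. On-treatment scans are 42 days apart, and the nominal gap from day 126 to day 195 is 69 days. Eligibility requires expected survival over 3 months and ECOG 0–2 and excludes brain metastasis, which should limit very early deaths.
- **That one inflation figure applies to both arms.** The last step of the working shows that it does not.
- **That the arithmetic proves bias from informative censoring.** Under constant hazards the log-rank comparison recovers the progression hazard ratio of 0.75 exactly. The calculation shows that a different quantity is being estimated. Dependence between death and progression is a plausible further problem that is not quantified here.
- **That the trial's main conclusion is at risk.** OS is primary, counts every death and is the endpoint behind the sample size.

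**Conclusion.** The point holds as an error of definition at moderate severity. As written, the endpoint called PFS is a time to progression, and deaths without documented progression would most naturally be censored, probably informatively.

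The size is unknown because f is not in the document. Under constant hazards, the median in an arm is overstated by 11% to 43% for f of 10% to 30% in that arm. In the assumed scenario the hazard ratio moves from 0.80 or 0.825 to 0.75. That is a modest shift unless the granules also affect death without progression. The primary analysis and the sample size do not change.

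**What to change.** Before database lock, replace the PFS sentence with: time from randomization to first RECIST 1.1 progression or death from any cause, whichever comes first; participants alive and progression-free are censored at their last evaluable scan. Keep the present definition only as a supportive analysis labelled time to progression. If the full protocol already counts death, bring the published sentence into line with it.

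The cost is one sentence in the protocol or analysis plan. No new data are needed, because survival state is already collected at every visit after baseline and OS requires the date of death. The change is cleanest now, while the analysts are still blinded; made after unblinding, it could look driven by the results.
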